### Metabolic status

Lipid profile along with 24-hour blood pressure monitoring will be analysed to further assess the response of these cardiometabolic risk factors to surgery. Continuous glucose measurement sensors or capillary glucose readings will be undertaken to give an alternative measure of glycaemic control.

### Body composition

All patients will undergo a whole body DEXA prior to and 15 months following surgery. This is a validated tool to estimate visceral adipose tissue.^53 54^

Where feasible, participants will undergo a gold standard assessment of visceral adipose tissue using MRI which will also quantify liver, muscle and pancreatic fat.

### DNA

Genomic DNA will be extracted from whole blood samples collected in an EDTA tube. A microarray customised to variants known to be associated with obesity, T2DM and fat patterning will be used to analyse samples. A weighted genetic risk score, with each variant weighted according to their previously published effect size, will be calculated individually.

### Omics

These will be used to explore possible mechanisms explaining the metabolic changes before and after surgery.

#### Transcriptomics/epigenomics/proteomics

Longitudinal tissue samples will be collected where possible and will undergo multi-omics assessment.

#### Microbiotal analysis

Longitudinal samples of stool will be collected to assess the microbiome.

#### Metabolomics

Longitudinal fasting urine and plasma metabolomic samples will be collected pre and following surgery.

### Predictors

Candidate predictors (for examples, see table 3) have been selected based on those identified in previous retrospective cohort studies. Two unique predictors, fat distribution and genetic risk score, will also be tested. We will then cautiously extend the model to address other factors in a univariate manner.

**Table 3 T3:** Candidate predictors of diabetes remission. V1 is study visit 1

Predictor	Units/categories	Variable type	Source data	Previous studies
Age	years	Continuous	Clinical history	46 47 56 57
BMI or weight	kg/m^2^ or kg	Continuous	V1	58 59
C-peptide	pmol/L	Continuous	Mixed meal test	46 56 60
Diabetes duration	years	Continuous	Clinical history	46 56 57 61–65
Fasting plasma glucose	mmol/L	Continuous	Blood test	66
Fat distribution	Visceral fat and android: gynoid fat	Continuous	DEXA, impedance, MRI	
Genetic risk score	Weighted genetic risk score	Categorical	DNA V1	
HbA1c with medications	mmol/mol	Continuous: will interact with medications since directly affected by them	Blood test	47 57 58 62–65 67–69
	Insulin, sulphonylureas, insulin sensitising agents, GLP-1 analogues, DPP-IV inhibitors, SGLT-2 inhibitors			
HOMA 2	Using interactive 24-variable assessment of homoeostatic model using default settings		Mixed meal test	70
Hypertension	Present/absent	Categorical	Medical history, 24-hour blood pressure monitoring	
	Controlled by 1–5 agents			
Insulinogenic index	δinsulin (0–30 min) / δglucose (0–30 min)	Continuous	Mixed meal test	
Presence of fatty liver disease as assessed by non-invasive markers	NAFLD liver fat score, fatty liver index, FIB-4	Categorical	Medical history, MRI, non-invasive markers including liver function tests	71
Presence of diabetes complications	Microvascular disease (including subgroups)	Categorical	Clinical history, microalbumin: creatinine, retinal imaging and clinical examination.	56
	Macrovascular disease (including subgroups)			
Presence of ectopic fat	% liver fat	Continuous	MRI	72
	% muscle fat			
	% pancreatic fat			
Sex	Male/female	Categorical	Clinical history	
TCI-R scoring	Novelty seeking, harm avoidance, reward dependence, persistence, self-directedness, cooperativeness and self-transcendence	Continuous	V1	
Waist:hip ratio	Measured in cm	Continuous	V1	

DPP-IV, Dipeptidyl peptidase-IV; FIB-4, Fibrosis-4 score; GLP-1, Glucagon-like peptide 1; HOMA, Homeostatic model assessment; MRI, magnetic resonance imaging; NAFLD, Non-alcoholic fatty liver disease; SGLT-2, sodium-glucose co-transporter-2; TCI-R, Temperament and Character Inventory-Revised.

A logistic regression model predicting diabetes remission assessed at the 15 months visit will be built using the prospective cohort data. This was chosen in preference to an ordinal regression approach, such as the proportional odds model, because of the need to have a clear and independent interpretation of the predictive contribution both to complete remission and to complete and partial remission. Logistic regression was preferred over another alternative approach, discriminant analysis, for the same reason and because logistic regression provides predicted probabilities for individual patients which can then be used within ROC curve analysis to provide estimates of sensitivity and specificity of the regression models measuring their accuracy to predict the diabetes remission outcome of metabolic surgery.

Initially, the effect of each of the clinical predictors and other covariates (patient demographic factors) of interest on each outcome is to be fitted in univariable models. Any clinical predictor that is significant at a threshold of p value≤0.20 will then be included in a multivariable model predicting the outcome of diabetes remission. Clinical predictors and other covariates will then be eliminated in a stepwise fashion until each remaining predictor is significant at the p value=0.05 threshold and the models are found to be stable. Pattern of fat storage will be measured by visceral adipose tissue (VAT) mass, SAT mass and VAT/SAT ratio, and genes influencing diabetes risk and fat deposition will be measured by the Genetic Risk Score using the approach of Fava *et al*.^51^ These will be added to the model, if not already included, to allow their association with diabetes remission to be formally quantified and tested. We will cautiously extend the model to address other factors in a univariate manner. Internal validation of the selection of the predictive model will be done using bootstrap sampling with re-application of the model selection procedure using at least 1000 replications. The performance of the prediction model under different scenarios will be assessed, primarily by obtaining fitted probabilities of remission from the model to estimate the area under the ROC curve, and also by demonstrating the sensitivity, specificity, positive predictive value and negative predictive value across a series of cut points representing a range of scenarios including high sensitivity, high specificity and equivalent sensitivity and specificity.

Survival curves will be plotted to show the proportion remaining free from diabetes over the longer-term according to categories of predictors identified to be important.

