## Introduction

Currently the majority of adults globally are obese or overweight. The increasing number of those with obesity is closely mirrored by the increasing prevalence of diabetes; at present over 400 million adults are estimated to be affected, 90% of whom have type 2 diabetes mellitus (T2DM).^1^ The close relationship between obesity, particularly ‘central’ or abdominal obesity, and T2DM has now been shown in multiple studies.^2 3^ Obesity, as defined by ethnicity-specific body mass index (BMI) cut-offs, is the principal modifiable risk factor for developing T2DM. However, the weight threshold at which T2DM develops varies between individuals, with significant variation among different ethnicities exemplifying two of the important factors that are thought to influence risk: the individual pattern of where fat is deposited in the body and underlying genetic predisposition.^4–9^

Epidemiological studies have shown those with a higher waist:hip ratio (WHR), representing centrally-deposited fat, are more likely to develop the disease.^3^ Central fat or higher intra-abdominal visceral fat deposition is known to be metabolically more damaging with increased likelihood of developing abnormalities in glycaemia, blood pressure and lipid profiles.^10^ However, it is not simply central adiposity but also ectopic fat that may have pathophysiological consequences.^11^ Evidence is accumulating regarding the detrimental effect on glycaemia from fat ectopically deposited within liver, skeletal muscle and pancreas.^12^

T2DM shows heritability and many pathogenic variants have been discovered which influence β cell functioning and insulin resistance.^13 14^ Moreover, genetic susceptibility to T2DM is known to be correlated with phenotypic changes in fat distribution: genetic variants associated with insulin resistance have been found to be correlated with lower subcutaneous adipose tissue (SAT) and a genetic predisposition to diabetes has been found in those with impaired SAT adipogenesis and increased waist circumference.^15^ Combining GWAS (genome-wide association study) data to derive personalised genetic risk, while challenging, has been successfully achieved in other conditions with the potential to add further precision to a predictive score.^16 17^

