### Sample size calculation

Using a logistic regression model to predict a 75% partial and completed diabetes remission rate from multiple predictors, a sample size of 150 provides 90% power at the two-sided 5% significance level to detect an OR of 2.0 per SD of any continuous predictor.^52^ This allows for up to 10% of the variation in any one predictor to be explained by the others in the model, and 15% loss to follow-up. The area under the receiver operating characteristic (ROC) curve, overall performance measure, will be estimated with a 95% CI width of at most±0.1 for an area above 0.65. With data analysed from 100 patients there would still be in excess of 80% power to detect the OR of 2.0, and a precision of at most±0.12 for the ROC curve area. This is reasonable enough to allow some deviation in assumptions, such as the dropout rate.

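### Table 3 types the weighted genetic risk score as categorical, though it is built as a continuous score, and the stated power does not cover it in that form

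*Protocol article*

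**What the plan says.** Table 3 (Predictors) gives the variable type as "Weighted genetic risk score Categorical". The other novel predictor, fat distribution, is typed as continuous in the same table. The DNA section explains how the score is built: "A weighted genetic risk score, with each variant weighted according to their previously published effect size, will be calculated individually".

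The score is central to the study. The Predictors section says "Two unique predictors, fat distribution and genetic risk score, will also be tested". After the stepwise selection it says of the fat measures and the genetic score: "These will be added to the model, if not already included, to allow their association with diabetes remission to be formally quantified and tested". The score therefore enters the model whether or not selection retains it. That text refers to a cited study for the method of scoring but does not say on what scale the score enters the regression.

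The Sample size calculation section sets out to "predict a 75% partial and completed diabetes remission rate from multiple predictors" and states that "a sample size of 150 provides 90% power at the two-sided 5% significance level" suffices "to detect an OR of 2.0 per SD of any continuous predictor". It allows for R² of 10% with the other predictors and 15% loss to follow-up, and it claims more than 80% power if 100 patients are analysed. It gives no power for any categorical predictor.

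**The concern.** A sum of weighted variants has no natural categories. Grouping it discards the variation within groups, makes the result depend on where the cuts fall and, if the groups enter as an unordered factor, spends extra degrees of freedom on the same hypothesis. The article does not say how many groups there are, where the cuts lie, or whether the groups would be scored as a trend. Those choices could therefore be made after the data are seen.

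The formal test of genetic risk is at stake. A reader who takes the 90% power as applying to both novel predictors would be relying on a figure calculated for a different form of the variable.

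**Working it through.** **Inputs from the Sample size calculation section:** remission p = 0.75; OR 2.0 per SD, so b = ln 2 = 0.6931; two-sided 5%; power 90%; R² = 0.10; 15% loss; 150 enrolled, so 150 × 0.85 = 127.5 analysed; fallback of 100 analysed.

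**Assumptions not in the documents:** the score is normally distributed; groups are of equal size; k = 2 to 5 groups.

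**Step 1: reproduce the plan's figure.** For a continuous covariate in logistic regression:

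n = (1.960 + 1.282)² / [p(1 − p)b²] = 10.507 / (0.1875 × 0.4805) = 116.6.

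Dividing by (1 − 0.10) gives 129.6, so 130. Dividing by 0.85 gives 153; multiplying by 1.15 instead gives 150. The stated 150 is reproduced to within 3%.

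Power = Φ(√[n(1 − R²)p(1 − p)] × b − 1.96):
- n = 127.5: Φ(4.639 × 0.6931 − 1.96) = Φ(1.255) = 89.5%.
- n = 100: Φ(4.108 × 0.6931 − 1.96) = Φ(0.887) = 81.3%.

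Both agree with the article for a continuous predictor.

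**Step 2: information kept after grouping.** Cut a standard normal score at its quantiles q₀ to q_k. The mean of group j is m_j = k[φ(q_{j−1}) − φ(q_j)], and the share of variance kept is the average of m_j². For an ordered trend with equally spaced scores s_j (centred at zero), the share is [mean(s_j m_j)]² / mean(s_j²).

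**Step 3: power.** The non-centrality for the continuous score is n × 0.9 × 0.1875 × 0.4805, which is 10.34 at n = 127.5 and 8.11 at n = 100. Multiply by the share kept. For the factor, use the non-central chi-square on k − 1 df. For the trend, use the formula in step 1 with 1 df.

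| Form of score | Share kept (factor / trend) | Factor, n = 127.5 | Trend, n = 127.5 | Factor, n = 100 | Trend, n = 100 |
|---|---|---|---|---|---|
| Continuous | 1 | 89.5% | – | 81.3% | – |
| 2 groups | 0.637 | 72.8% | same | 62.2% | same |
| 3 groups | 0.793 / 0.793 | 72.9% | 81.7% | 61.6% | 71.8% |
| 4 groups | 0.861 / 0.856 | 70.6% | 84.5% | 58.8% | 75.0% |
| 5 groups | 0.897 / 0.888 | 67.8% | 85.8% | 55.8% | 76.5% |

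The continuous row is a single 1-df test. For the median split, for example: 10.34 × 0.637 = 6.58; √6.58 − 1.96 = 0.605; Φ(0.605) = 72.8%.

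**Step 4: the same loss in patients.** By the same formulas, with division by 0.85 for loss, 90% power needs about 231 to 249 enrolled for an unordered factor of two to five groups and 172 to 193 for a trend over three to five groups. The continuous score needs 153 on the same basis.

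**Step 5: simulation check.** I ran 2,500 data sets with n = 127, overall remission 75%, one covariate correlated with the score at R² = 0.10, and likelihood-ratio tests. Power was 85% for the continuous score, 76–78% for a trend over three or four groups, and 62–65% for a factor of two to five groups. The levels are lower than the closed-form approximation gives, but the ordering is the same and the gaps are similar or slightly larger.

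**The case against.** **The sample size is not wrong.** A reader might infer that the plan breaches its own power claim. The document does not support that. The claim is limited to continuous predictors, and for those it reproduces. It is silent on the score as Table 3 types it.

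**The entry may be a slip or a display choice.** The article plans survival curves by categories of predictors, and the cited scoring approach, which is not shown, may define groups. Both are possible. If the entry is a slip, correcting one word settles it. If grouping is intended, the article still gives no groups and no power for them. Curves by group do not require a grouped term in the regression.

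**The loss may be small.** This stands in part. With a trend over four or five groups, power is only about 4 to 5 points below the continuous analysis (89.5% against 84.5% and 85.8%). However, nothing specifies a trend, and an unordered factor is the usual reading of a categorical variable.

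**Two wider readings do not hold.** A reader might extend the point to the liver scores in Table 3, but that row concerns whether fatty liver disease is present, which is a categorical construct. A reader might also infer from Table 3 that ethnicity is left out of the model testing the genetic score. The table is offered only as examples, and the modelling text also fits patient demographic factors, so absence from the table does not show omission. The documents give no figures from which to size any confounding by ancestry.

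**Conclusion.** The point holds in a narrow form. The Table 3 entry does not fit the construction described in the DNA section, it is unexplained, and it concerns a predictor singled out for formal testing. The 90% power does not carry over to the score as typed.

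For an OR of 2.0 per SD at the planned analysed number, grouping lowers power from 89.5% by about 4 to 8 points as a trend over three to five groups, and by about 17 to 22 points as a median split or unordered factor. At 100 analysed, 81% becomes 72–77% (trend) or 56–62% (factor) over three to five groups. These ranges rest on a normal score, equal-sized groups and the article's own 75% remission and R² of 0.10. The number of groups is unknown, so no single figure can be given. The direction does not depend on it: every grouping examined has less power than the continuous score.

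**What to change.** Change the variable type of the genetic risk score in Table 3 to continuous. State in the Predictors section that it enters the logistic model per SD, and restrict groups to display, such as the survival curves. The sample size statement then covers the score as written.

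If grouping is deliberate, give the reason, fix the number of groups and the cut points in advance, say whether they enter as a factor or a trend, and state the power for that analysis.

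The cost is one table entry and one sentence. No new data or extra patients are needed.

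### Screening at p≤0.20 and stepwise elimination over some 36–42 candidate coefficients, with about 32 non-remitters and no stated shrinkage or calibration step, will give an over-fitted model whose predicted probabilities are too extreme

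*Protocol article*

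**What the plan says.** The primary objective is to develop and internally validate a model that predicts remission. The Predictors section fixes how it is built:

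- **Screen:** "Any clinical predictor that is significant at a threshold of p value≤0.20 will then be included in a multivariable model".
- **Elimination:** terms are then "eliminated in a stepwise fashion until each remaining predictor is significant at the p value=0.05 threshold", and the models must also prove stable.
- **Forced terms:** VAT, SAT, VAT/SAT and the genetic risk score are added afterwards if not already in, so that their association with remission can be formally tested.
- **Validation:** a bootstrap of at least 1000 replications repeats the whole selection. Performance is judged mainly by ROC area, with sensitivity, specificity and predictive values at several cut points. No calibration measure and no shrinkage of coefficients is stated.

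Table 3 has 17 rows, given as examples. Several hold more than one term. The HbA1c row, for instance, lists six drug classes and says "Continuous: will interact with medications since directly affected by them".

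The Sample size calculation says that "a sample size of 150 provides 90% power at the two-sided 5% significance level to detect an OR of 2.0 per SD", at 75% partial plus complete remission, with 10% of a predictor's variation explained by the others and 15% loss to follow-up.

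**The concern.** The information in a binary outcome is limited by its rarer class, here the non-remitters. When many candidates compete for few such patients and are chosen by p-value, the terms that survive are partly those whose estimates happened to be large in this sample. Their coefficients are too big, and the predicted probabilities too far from the average.

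This bears directly on the stated purpose. The article prefers logistic regression partly because it yields a probability for each patient, and the abstract intends the work to help prioritise surgery. A model that ranks patients acceptably can still give the wrong probability. The fat-distribution measures and genetic score would also be tested alongside an adjustment set that is itself partly a product of chance.

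**Working it through.** **1. The plan's own figure.** For one continuous predictor, n = (z₀.₉₇₅ + z₀.₉₀)² / [p(1−p)(ln OR)²], divided by (1−R²) and then by (1−loss). With p = 0.75, OR = 2.0, R² = 0.10 and loss = 0.15:

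- 10.507 / (0.1875 × 0.4805) = 116.6
- 116.6 / 0.90 = 129.6
- 129.6 / 0.85 = 152.5 (129.6 × 1.15 gives 149.0)

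The stated 150 is reproduced to within 3%. Power is 89.5% with 127.5 analysed and 81.3% with 100, in line with both statements in the article. The calculation concerns one OR in a given model, not selection among dozens of terms.

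**2. Non-remitters.** 150 × 0.85 = 127.5 analysed, and 127.5 × 0.25 = 31.9. With no loss the figure is 37.5; with 100 analysed it is 25.

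**3. Candidate coefficients in Table 3.**

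| Rows | Coefficients |
|---|---|
| Age, BMI or weight, C-peptide, duration, fasting glucose, genetic score, HOMA 2, insulinogenic index, sex, waist:hip ratio | 10 |
| HbA1c (1), drug classes (6) | 7 |
| TCI-R scales | 7 |
| Ectopic fat sites | 3 |
| Fatty liver scores | 3 |
| Fat distribution | 2 |
| Hypertension | 2 |
| Complications | 2 |
| **Subtotal** | **36** |
| HbA1c-by-drug interactions | 6 |
| **Total** | **42** |

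**4. Non-remitters per candidate.** 31.9/42 = 0.76; 31.9/36 = 0.89; 31.9/17 = 1.9. For complete remission, assume that the 4 in 10 quoted for 1 year also holds at 15 months. Then there are 127.5 × 0.40 = 51 remitters, and 51/42 = 1.2.

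**5. Simulation of the stated rule.** Assumptions: n = 127, 75% remission, standard normal candidates with pairwise correlation 0.2, five true predictors (OR 2.0, 1.5, 1.5, 1.4, 1.4 per SD), screen at p≤0.20, elimination to p=0.05. Ranges cover repeated runs.

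| | 17 candidates | 40 candidates |
|---|---|---|
| Noise share of retained terms | about 20% | about 43% (42–48%) |
| Runs with a noise majority | 7% | 25–28% |
| Median calibration slope, new data | 0.66–0.70 | 0.54–0.56 |
| ROC area, new data | 0.74 | 0.72–0.73 |

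With 40 candidates the apparent ROC area was 0.83. With 25 candidates the slope was 0.60–0.61. With 40 candidates and 40% complete remission it was 0.60–0.61, and with uncorrelated candidates 0.34–0.35.

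**6. Sensitivity to the assumptions.** With 42 candidates, n = 128, correlation 0 or 0.1, and three, five or eight true predictors at OR 2.0 or five or eight at OR 1.5, the slope was 0.27–0.55. The noise share was 26–53%, and apparent ROC area exceeded new-data ROC area by 0.10–0.19. With 36 uncorrelated candidates the slope was 0.33–0.52.

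**7. What a slope of 0.55 means.** Take a patient predicted 2 log-odds units below the 75% average (log-odds 1.10 − 2 = −0.90, or 29%). If calibration is right at the average, the true value is 1.10 − 0.55 × 2 = 0.00, or 50%. At slope 0.70 it is 1.10 − 1.40 = −0.30, or 43%.

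**The case against.** The best defence is the bootstrap. Repeating the full selection in every replicate is good practice and gives an honest estimate of ROC-area optimism. The article also requires stable models, calls the study preliminary, says external validation is needed, and aims to find covariates for larger studies. This stands as far as reporting of discrimination goes. But measuring optimism does not shrink the coefficients, and no stated step does so.

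The count of 42 is the widest reading. It includes the interactions and three liver scores. It also includes fat distribution and the genetic score, which enter whatever their p-value, and MRI fat, which is measured only where feasible. That is fair, but with 17 single terms the slope is still only about 0.70.

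Three stronger readings are tempting and are not supported:

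- **The rule would mostly select noise.** With true predictors present, noise is usually a minority of the retained terms. It dominates only if real effects are few or weak.
- **The rule itself discards true predictors.** In the simulation it missed 3.0–3.1 of five, but a model holding only the five true predictors, tested at p<0.05, also missed 3.1. That mainly reflects the sample size and the assumed ORs of 1.4–1.5, below the OR of 2.0 for which the study is sized.
- **A fix would clearly raise the ROC area.** Ridge on all 40 candidates gained about 0.01 (0.74 against 0.73). A seven-variable core gave about 0.75 when it held the strong predictor and 0.71–0.72 when it did not.

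Finally, ridge coefficients are biased and lack standard tests, whereas the article wants fat distribution and genetic score formally tested. The fix has to allow for this.

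**Conclusion.** The concern holds as a problem of over-fitting and calibration. The selection rule is stated text and produces the primary result, with 0.76–0.89 non-remitters per candidate coefficient, or 1.9 on the narrowest reading of Table 3. Under the main assumptions the new-data calibration slope is about 0.55 with 40 candidates and 0.70 with 17, and about 43% and 20% of retained terms are noise. The number, strength and correlation of the true predictors are assumptions. They move the size of the effect, but every scenario with true predictors gave a slope well below 1.

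A reader might infer that the sample size is wrong. It is not: the figure of 150 reproduces, and it answers a different question from the one the selection rule raises.

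**What to change.** **Primary model.** Replace the p≤0.20 screen and the stepwise step with a pre-specified core of about 6–8 coefficients taken from the cohorts cited in Table 3, kept whatever their p-values. Add one fat-distribution measure and the genetic risk score. Fit by ridge-penalised logistic regression, with the penalty chosen inside each replicate of the bootstrap already planned.

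**At minimum.** Limit the candidate list, multiply the coefficients by the shrinkage factor from that bootstrap, and re-estimate the intercept.

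**Reporting.** Give the optimism-corrected calibration slope and intercept beside the ROC area.

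**Formal tests.** Test fat distribution and genetic score in an unpenalised model adjusted for the same core, so that the stated aim is kept. Label the remaining Table 3 candidates exploratory.

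Penalising or shrinking brings the slope to about 0.9–1.1 in simulation.

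**Cost.** Changed analysis wording and a little more programming, with no added patients or visits. Fewer candidates compete for the primary model, and novel covariates are reported as exploratory.

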### Predicting diabetes remission following surgery

There is a substantial disparity between the numbers eligible for metabolic surgery and the resources available to deliver it; in the UK 2 million people fulfil the criteria but surgery is only being performed in 5600 patients per year.^42^ Furthermore, there is variation in the metabolic response between individuals such that less than half are expected to have complete diabetes remission at 1 year following surgery. If we can better predict who will benefit from surgery by remission of diabetes we can better inform patients and direct the surgery to where it will be most effective.^43^ Currently in the UK, BMI cut-offs dictate eligibility for surgery, along with more recently introduced diabetes duration and ethnicity criteria.^44^ However, baseline BMI does not correlate well with the likelihood of diabetes remission thus other predictors are necessary to better inform eligibility based on intended benefit.^45^

Predictive factors have been found in multiple, mainly retrospective studies and some have been incorporated into models of diabetes remission.^46–48^ These models have tried to predict diabetes remission based on easily available clinical data making them translatable to everyday practice. However, they remain limited in their clinical applicability.^49^ Moreover, none have incorporated fat distribution or genetic risk factors which have important aetiopathological roles in T2DM. Furthermore, they are, in most cases, based on retrospective studies. One problem faced in this instance is that the consensus definition of diabetes remission depends on withdrawal of pharmacological therapies for T2DM for 1 year. There is often no standardised pathway to assess the remission status after surgery, which can lead to differing practice among clinicians thus hampering the ability to define remission status with accuracy.

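### Fat distribution and the genetic risk score get only an association test, with no guaranteed model without them and no stated measure of how much they improve prediction

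*Protocol article*

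**What the plan says.** The Predictors section describes a sequence. Clinical predictors and demographic covariates are fitted one at a time, those with p ≤ 0.20 go into a multivariable logistic model, and stepwise elimination continues until all that remain meet p = 0.05. VAT mass, SAT mass, VAT/SAT and the Genetic Risk Score come next: "These will be added to the model, if not already included, to allow their association with diabetes remission to be formally quantified and tested".

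Table 3 nevertheless lists fat distribution and the genetic risk score among the candidate predictors, while the text above it presents them as two further predictors to be tested. Performance (AUC, sensitivity, specificity and predictive values, with a bootstrap of at least 1000 replications that repeats the selection) is described for the prediction model. No section compares a model with these markers to one without them.

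The primary objective is to develop and internally validate a predictive model. The section on predicting remission says of existing models that "none have incorporated fat distribution or genetic risk factors which have important aetiopathological roles in T2DM". The Introduction describes combined genetic risk, on the strength of other conditions, as "with the potential to add further precision to a predictive score".

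**The concern.** The rationale is about what is added: existing models rest on easily available clinical data, and this study brings in two things they lack. The matching question is how much better patients are classified once those two things are known. The stated analysis gives a coefficient and a p value, which is a different quantity. A marker can be clearly associated with remission and change the predicted probabilities little.

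The conditional clause adds a second problem. If a fat measure survives stepwise elimination, its p value follows selection at 0.05 and leans towards significance. It may also have displaced correlated candidates such as waist:hip ratio, BMI or liver fat, so deleting it afterwards does not recover the model that clinical data alone would have given.

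At stake is a report that fat distribution or genotype predicts remission, with nothing to show whether DEXA or genotyping improves prioritisation for surgery.

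**Working it through.** **1. What the study is sized for.** Inputs from the Sample size calculation section: "a sample size of 150 provides 90% power", "at the two-sided 5% significance level", "to detect an OR of 2.0 per SD of any continuous predictor", the aim to "predict a 75% partial and completed diabetes remission rate from multiple predictors", and an allowance for "up to 10% of the variation in any one predictor to be explained by the others in the model, and 15% loss to follow-up".

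Formula for one continuous predictor in logistic regression: n = (z₀.₉₇₅ + z₀.₉₀)² / [p(1−p)(ln OR)²] / (1−R²).

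- (1.960 + 1.282)² = 10.507
- p(1−p) = 0.75 × 0.25 = 0.1875; (ln 2)² = 0.4805; product 0.0901
- 10.507 / 0.0901 = 116.6; divided by 0.90 = 129.6 analysed
- 129.6 / 0.85 = 152.5 recruited, against 150 stated (1.6% apart)
- With 150 × 0.85 = 127.5 analysed, power is 89.5%; with 100 analysed, 81.3% (stated as above 80%)

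The Hanley–McNeil half-width of the 95% CI for one AUC of 0.65 is 0.096 with 150 patients, 0.104 with 127.5 and 0.118 with 100, in line with the stated ±0.1 and ±0.12. The sample size section is sound. It concerns an odds ratio and a single AUC, not a difference between two models.

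**2. What such an odds ratio is worth in AUC.** The document gives no expected AUC for the clinical model, so this part rests on assumptions: 75% remission, one normal clinical score with coefficient 0.6, 1.0 or 1.5 per SD, and one normal marker sharing R² = 0.10 with it. True AUCs come from 400,000 simulated patients. Power and the SD of the apparent (uncorrected) gain come from 400 simulated studies of 127 patients per setting.

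| Marker OR per SD | AUC without → with marker | Gain | SD of apparent gain | Power of nested likelihood-ratio test |
|---|---|---|---|---|
| 2.0 | 0.695 → 0.752 | 0.057 | 0.038 | 0.87 |
| 2.0 | 0.765 → 0.803 | 0.038 | 0.028 | 0.80 |
| 2.0 | 0.830 → 0.853 | 0.024 | 0.020 | 0.74 |
| 1.5 | 0.683 → 0.708 | 0.025 | 0.030 | 0.42 |
| 1.5 | 0.759 → 0.775 | 0.015 | 0.022 | 0.42 |
| 1.5 | 0.827 → 0.837 | 0.009 | 0.014 | 0.35 |

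The effect the study is powered to detect is thus compatible with a gain of 0.02 to 0.06.

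**3. Which statistic should carry the formal test.** Simulations with the same 127 patients, 75% remission and R² = 0.10 compared the nested likelihood-ratio test with a 95% bootstrap CI for the optimism-corrected AUC difference. At OR 2.0 the test was significant in about 70–88% of runs, while the CI excluded zero in only about 8–11%. At OR 1.5 the figures were about 36% and 1%. The AUC difference describes the size of the gain but is a weak test of whether there is one.

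These runs use one marker at a time (one degree of freedom). A joint test of VAT, SAT, VAT/SAT and the genetic score has more, and its power will differ.

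**The case against.** A reader might infer that the study cannot say whether these markers improve on clinical data. The document does not support that.

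- A marker added last is tested conditional on the retained predictors, and in nested logistic models that is a valid test of whether it carries extra information.
- If no marker was selected earlier, the stepwise model before the addition is itself the comparator, in the same cohort. The screening sentence names clinical and demographic variables, so this may be the intended route. The data would then allow AUC with and without the markers.
- The section on predicting remission sets the ultimate aim as finding novel covariates whose predictive power is studied further in larger studies, and the study calls itself preliminary.
- The article is condensed, and the choice of models that receive an AUC may be left to a fuller plan.

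A reader might also infer that the AUC difference should be the primary evidence, because the gains are smaller than the half-width of a single AUC. Step 3 argues against this: its interval would seldom exclude zero.

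What remains is narrower. The validity argument fits the case where markers are added last, and the conditional clause with Table 3 leaves the other case open. The Predictors section is specific about thresholds, elimination, bootstrap and cut points, and at that level of detail it states association as the purpose of the marker step. That is a stated rule that can be improved, not just a missing detail.

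**Conclusion.** The concern holds in limited form and should be addressed, though it does not invalidate the study. The plan tests association only, and its entry rule guarantees neither a marker-free comparator nor a test of the markers unaffected by selection. A significant odds ratio would leave the improvement in prediction unquantified. At OR 2.0 per SD that improvement would be about 0.02 to 0.06 in AUC, and at OR 1.5 about 0.01 to 0.025.

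These sizes depend on the assumed clinical-model AUCs (about 0.70 to 0.83), a single normal clinical score and R² = 0.10 between score and marker. The point about the entry rule follows from the text alone.

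**What to change.** Amend the Predictors section as follows.

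1. Keep VAT, SAT, VAT/SAT and the genetic risk score out of the univariable screen and the stepwise elimination.
2. Select the base model from the other Table 3 candidates, and state which of them count as clinical. Table 3 mixes routine data with mixed meal indices, MRI ectopic fat, android:gynoid fat, waist:hip ratio and TCI-R scores, and several of these overlap with fat distribution.
3. Add the markers to that base model in the same patients, and use the nested likelihood-ratio test as the formal test.
4. As a secondary, descriptive measure, report optimism-corrected AUC with and without the markers, and the difference with a bootstrap CI, inside the bootstrap already planned.

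The cost is one extra model per bootstrap replication, with no new data or patients. The CI for the AUC difference will be wide and will often include zero at this sample size, so the text should say in advance that an interval including zero does not show absence of gain.
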